## Abstract

**Objective::**

To explore the influence of the education of lifestyle in the type 2 diabetes mellitus (T2DM) patients with microalbuminuria as a part of the enhanced multifactorial intervention.

**Methods::**

This study will be conducted from May 2021 to August 2022 at Ningbo No.6 hospital. The experiment was granted through the Research Ethics Committee of Ningbo No.6 hospital (539D035). The patients will be included if they are between 18 and 65 years old and are diagnosed with T2DM with microalbuminuria and the patients who have signed the written informed consent. While the patients will be excluded if they have serious physical comorbidities and patients who are unwilling to offer the informed consent to take part in this experiment. We measure the clinical examination (fasting blood-glucose, glycosylated hemoglobin and routine urine test) timely. Detail of daily dietary intake and lifestyle factors are also recorded.

**Results::**

Table 1 reflects the comparison of the biochemical and clinical variables and the lifestyle factors.

**Conclusion::**

Lifestyle education is effective in facilitating the control of T2DM and reducing microalbuminuria.

**Trial registration number::**

researchregistry6348.

## Introduction

1

Type 2 diabetes mellitus (T2DM) is regarded to be one of the most prevalent diseases worldwide.^[1,2]^ For the T2DM, its etiology is complex, which is related to the reversible factors (for instance, smoking, physical activity and diet) and the irreversible risk factors (for instance, genetics, age, ethnicity and race).^[3,4]^ Due to the urbanization, the aging of the population, and the changes of lifestyle, the prevalence of diabetes mellitus is rising rapidly in the world. In the past 30 years, the number of diabetes mellitus people in the world has more than doubled.^[5]^ In 2010, approximately 285 million people suffered from diabetes mellitus in the world, 90 percent of these patients were T2DM. It is estimated that by 2030, the number of diabetes mellitus patients worldwide will increase to 439 million.^[6]^ Diabetic nephropathy is one of the most feared and prevalent complications of T2DM.^[7]^ With the increasing burden of diabetes in the world, an increasing number of diabetic nephropathy patients have emerged. It is also related to the increased mortality rate, and is one of the most familiar causes of renal replacement therapy and end-stage renal disease. Mental stress, inadequate physical activity and improper diet are regarded as the main components of the unhealthy lifestyle, which are the significant factors leading to the onset of T2DM.^[8–10]^ Recently, more and more studies have emphasized the value of lifestyle education in patients with T2DM ^[11,12]^ and the certificated diabetes educator is considered an important member of the multidisciplinary team responsible for patient care. Education of lifestyle for patients with T2DM is primarily carried out in hospitals. Nevertheless, offering education in the outpatient department should effectively improve the participation of T2DM patients in the education of lifestyle. Currently, the efficacy of lifestyle education in T2DM with microalbuminuria has not been consistently demonstrated. Therefore, the purpose of this protocol is to explore the influence of the education of lifestyle in the T2DM patients with microalbuminuria as a part of the enhanced multifactorial intervention.

## Methods

2

This study will be conducted from May 2021 to August 2022 at Ningbo No.6 hospital. The experiment was granted through the Research Ethics Committee of Ningbo No.6 hospital (539D035) and recorded in research registry (researchregistry6348). The random numbers sequence is produced through the computer. The random numbers are hidden by the sequentially numbered opaque and sealed envelopes. The patients will be randomly assigned into the study group and control group and each group includes 50 patients. The duration of follow up is 2 months.

### Inclusion and exclusion criteria

2.1

Patients will be included in this experiment if their ages are in the range of 18 to 65 years old and are diagnosed with T2DM with microalbuminuria and the patients who have signed the written informed consent. While the patients will be excluded if they have serious physical comorbidities and patients who are unwilling to offer the informed consent to take part in this experiment.

### General education

2.2

A detailed explanation of the pathogenesis of diabetes, use of medications and the effect of self-monitoring devices are provided to address patients concerns and queries. The family members of patients are encouraged to help monitor the medication compliance.

### Diet

2.3

Prior to randomization, all patients are informed of the fundamental principles of diabetes diet. The goal of the study group is to achieve permanent changes in the quantitative and qualitative dietary fat by a low intake of saturated fatty acids, the high intake of monounsaturated fatty acids and polyunsaturated fatty acids and increasing the intake of the complex carbohydrates. The whole team provides a large number of personal dietary consultations. Consultations are the personal interviews. The patients risk profile is discussed and the individual goals for smoking cessation, exercise, and diet are set and modified in collaboration with patient. The topics include smoking, exercise and diet habits, combined with the discussions of lifestyle habits, beliefs and attitudes. The method of education is on the basis of the patients needs.

### Exercise

2.4

Exercise refers to the physical activities other than daily chores and work activities. Through the educational exercises and positive feedback, for instance, proving that moderate physical exercise can immediately reduce blood glucose, thus prompting patients to start or continue to exercise.

### Smoking habits

2.5

All the smokers and their spouses in study group are invited to participate in the programs of standardized smoking cessation. The project is carried out in the form of group consultations with a maximum of 14 participants. Patients are educated about the benefits of quitting smoking, and the specific advice on how to cope with the temptation to start smoking again, containing the information on the substitutes of nicotine, which is provided free of charge.

### Outcomes

2.6

We measure the clinical examination (fasting blood-glucose, glycosylated hemoglobin and routine urine test) timely. Detail of daily dietary intake and lifestyle factors are also recorded.

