## Results

3

Table 1 reflects the comparison of the biochemical and clinical variables and the lifestyle factors.

**Table 1 T1:** Comparison of the biochemical and clinical variables and the lifestyle factors.

	Study group (n = 50)	Control group (n = 50)	*P* value
Body weight			
Current smokers			
Glycosylated hemoglobin			
Fasting blood-glucose			
Energy intake			

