## Conclusion

4

Lifestyle education is effective in facilitating the control of T2DM and reducing microalbuminuria.

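### The conclusion claims a reduction in microalbuminuria, but no albumin measure is named as an outcome and no row of Table 1 concerns urine

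*Protocol article*

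**What the plan says.** Patients enter the trial because they are "diagnosed with T2DM with microalbuminuria" (section 2.1). The Introduction gives as the reason for the study that "the efficacy of lifestyle education in T2DM with microalbuminuria has not been consistently demonstrated", and states that "the purpose of this protocol is to explore the influence of the education of lifestyle in the T2DM patients with microalbuminuria".

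Section 2.6 gives the outcomes in two sentences: "We measure the clinical examination (fasting blood-glucose, glycosylated hemoglobin and routine urine test) timely", and "Detail of daily dietary intake and lifestyle factors are also recorded".

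Section 3 presents an empty table of the planned "comparison of the biochemical and clinical variables and the lifestyle factors". Its five rows are body weight, current smokers, glycosylated hemoglobin, fasting blood glucose and energy intake, with columns for the two groups of 50 and a P value.

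Section 4, like the abstract, concludes: "Lifestyle education is effective in facilitating the control of T2DM and reducing microalbuminuria".

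**The concern.** The conclusion makes two efficacy claims. A reader who looks for the comparison behind each one finds glycosylated hemoglobin and fasting glucose for the first. For the second there is only a urine test of unspecified content, and it does not reappear in the results table.

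If the trial is run and reported as the article sets out, the statement about microalbuminuria would stand without a group difference, an interval or a P value, however the table cells are filled. The loss could be permanent, because an albumin value not obtained at baseline cannot be recovered after follow-up.

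**Working it through.** The defect is a mismatch of text, so the main check sets the sections side by side.

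| Claim in section 4 | Outcome named in 2.6 | Row in Table 1 |
|---|---|---|
| Control of type 2 diabetes | Fasting glucose, glycosylated hemoglobin | Both present |
| Less microalbuminuria | Routine urine test; no albumin measure, unit or time point | None |

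- **Outcomes.** One of the three named examinations is a urine test. No albumin concentration, excretion rate or albumin-to-creatinine ratio is named anywhere in the article.
- **Table rows.** 0 of 5 concern urine or albumin. The urine test in 2.6 is the only one of the three examinations without a row.

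**The plan's own figure.** The article gives 50 patients per group, without an effect size, standard deviation or power. It can be neither reproduced nor refuted, and this point does not depend on it.

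**Illustration of the remedy only.** These figures show what a quantitative albumin outcome could detect in a trial of this size. They do not measure the defect. From the article: 50 per group and a significance level of 0.05. Assumed: a two-sided test, 80% power, a standard deviation of 0.5 to 0.8 on the log scale, and a correlation of 0.5 to 0.7 between baseline and follow-up.

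1. Unadjusted two-sample *t* test: the detectable difference is 0.566 SD. The normal approximation gives nearly the same: (1.960 + 0.842) × √(2/50) = 2.802 × 0.2 = 0.560.
2. As a ratio of geometric means, exp(−0.566 × SD):
   - SD 0.5: exp(−0.283) = 0.754, a reduction of about 25%
   - SD 0.8: exp(−0.453) = 0.636, a reduction of about 36%
3. With baseline adjustment, multiply by √(1 − r²):
   - r = 0.5: 0.566 × 0.866 = 0.490 SD
   - r = 0.7: 0.566 × 0.714 = 0.404 SD
4. As ratios, at the two ends of the range:
   - r = 0.7, SD 0.5: exp(−0.202) = 0.817, a reduction of about 18%
   - r = 0.5, SD 0.8: exp(−0.392) = 0.676, a reduction of about 32%

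The range of 18% to 32% belongs to the baseline-adjusted analysis recommended below. The range of 25% to 36% belongs to an unadjusted comparison.

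**The case against.** **Microalbuminuria only defines the population.** This is right for the objective. The Introduction and abstract ask about the influence of education in patients who have microalbuminuria, and do not name its reduction as the endpoint. A reader might infer that the trial cannot answer its own question. The documents do not support that, because the glycaemic part is both measured and tabulated. What remains is that the conclusion itself turns microalbuminuria into an efficacy claim.

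**A routine urine test may include albumin.** It may. Patients need a diagnosis of microalbuminuria to enter, so some albumin assessment must exist at or before entry, and an article may leave the assay to a fuller protocol. A reader might infer a dipstick that cannot quantify albumin in this range, but that is an assumption and the article does not say so. The missing table row does not depend on it.

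**Table 1 need not be the whole analysis.** Section 2.7 speaks of analysing all the data, so it would go too far to say that no urine result will ever be compared. But that general statement names no albumin variable, and the only table the article sets out leaves urine out.

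**Body weight is also in the table but not in 2.6.** This mismatch is minor. Weight can be read as part of a clinical examination or of the lifestyle factors, and nothing here rests on it.

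**The conclusion is printed before there are results.** True, since the table cells are empty, but that is a separate matter. Filling every cell would still leave the albuminuria claim unsupported.

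**Conclusion.** The point holds for one of the two claims in the conclusion. The article states its outcomes, its table and its conclusion, and for microalbuminuria they do not agree: no albumin measure is named, 0 of 5 planned rows concern urine, and a reduction is claimed all the same. This is a contradiction within the article and not a detail left to an unseen document, because a fuller protocol would not make the printed table support the printed conclusion.

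This verdict needs no assumption about the urine assay, the standard deviation or the power. It does not extend to the glycaemic claim, nor to the trial's objective as worded. As long as the claim stays in the conclusion, the mismatch must be corrected.

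**What to change.** Either of two changes resolves it.

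1. **Measure it.** In 2.6, name a quantitative urine albumin outcome, for example the urine albumin-to-creatinine ratio, with its unit, at baseline and at 2 months in both groups. Add it as a row of Table 1. Compare the groups on the log scale with adjustment for the baseline value, and report the geometric mean ratio with its 95% confidence interval.
2. **Withdraw the claim.** If albumin is not to be measured, remove the statement about microalbuminuria from the conclusion in both the abstract and section 4.

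The first option costs 2 groups × 50 patients × 2 time points = 200 inexpensive assays, one table row and a sentence in 2.6. This assumes that urine is collected at both time points; section 2.6 does not give the schedule. If it is not, the extra collection is a further cost. The second option is a change of wording only.

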### Statistical analysis

2.7

Through utilizing the Microsoft Excel 2013, the data is recorded, and the analysis of all the data is carried out through utilizing IBM SPSS Statistics for Windows, version 20 (IBM Corp., Armonk, NY, USA). With the χ^2^-tests and independent *t* tests, the analysis for continuous variables and categorical variables are implemented respectively. All data are described with proper features, such as percentage, average and median. *P* value less than .05 indicates that there is statistical significance.

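### Section 2.7, read literally, assigns χ² tests to continuous variables and t tests to categorical ones; probably a transposition, but nothing corrects it and four of five Table 1 rows depend on it

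*Protocol article*

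**What the plan says.** The protocol article gives its inferential method in one sentence of section 2.7 (Statistical analysis): "With the χ^2^-tests and independent *t* tests, the analysis for continuous variables and categorical variables are implemented respectively". The same section sets the significance threshold at 0.05 and lists percentage, average and median as descriptive summaries.

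On design, the Methods section says "The patients will be randomly assigned into the study group and control group and each group includes 50 patients". Section 2.6 (Outcomes) says "We measure the clinical examination (fasting blood-glucose, glycosylated hemoglobin and routine urine test) timely" and gives no categories or cut-points for the two glycaemic measures.

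Table 1 in the Results section is an empty shell with a P value column and five rows. Four are continuous: body weight, "Glycosylated hemoglobin", fasting blood-glucose and energy intake. One is categorical: "Current smokers".

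**The concern.** The order of the words in section 2.7 matters because *respectively* fixes the pairing. The first test named (χ²) goes with the first data type named (continuous), and the second (t) with the second (categorical). A t test compares means and uses the size of the difference between groups. A Pearson χ² test on the recorded values treats each distinct value as an unordered label, so it ignores both order and distance.

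This is a positive statement that is wrong, not a detail left for later. It covers the two glycaemic measures named as outcomes. An analyst who follows the text obtains P values that say little about the intervention in four of five rows. An analyst who uses the t test departs from the published protocol. In neither case can a reader rely on the stated method.

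**Working it through.** **Inputs from the document.** 50 patients per group, 100 in total (Methods); threshold 0.05 (section 2.7; sidedness is not stated, two-sided assumed); four continuous rows and one categorical row (Table 1).

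**Inputs that are assumptions.** The document gives no SD, effect size or recording precision. The check uses normal data with the SDs and rounding shown below, and standardised differences d = 0, 0.5 and 0.8. There is no stated power figure to reproduce; the 50 per group is given without a derivation.

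**Step 1. χ² when all values differ.** Each distinct value is one row of a 100 × 2 table, with observed counts 1 and 0 and expected counts 0.5 and 0.5. Its contribution is

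(1 − 0.5)²/0.5 + (0 − 0.5)²/0.5 = 0.5 + 0.5 = 1.

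Summing over 100 rows gives χ² = 100 on (100 − 1)(2 − 1) = 99 df, so P = 0.453. Group means do not enter, so the result is the same for any treatment effect and power is 0. This step needs no SD or effect size, only that no two values tie.

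**Step 2. t test benchmark.** The noncentrality is d × √(n/2) = d × √25 = 5d, on 98 df. At d = 0.5 it is 2.5 and power is 0.697. At d = 0.8 it is 4.0 and power is 0.977.

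**Step 3. Values with ties, by simulation.** 2,000 trials per setting, 50 per group. Entries are the proportion of trials with P < 0.05.

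| Variable (assumed SD, rounding) | d | χ², ungrouped | t test | χ² after median split |
|---|---|---|---|---|
| HbA1c (1.2, 0.1) | 0.5 | 0.010 | 0.694 | 0.538 |
| HbA1c (1.2, 0.1) | 0.8 | 0.047 | 0.974 | 0.897 |
| HbA1c (1.0, 0.1) | 0.5 | 0.034 | 0.712 | 0.561 |
| HbA1c (1.0, 0.1) | 0.8 | 0.073 | 0.983 | 0.899 |
| Fasting glucose (2, 0.1) | 0.5 | 0.006 | 0.700 | 0.546 |
| Fasting glucose (2, 0.1) | 0.8 | 0.009 | 0.979 | 0.908 |
| Weight (12, 0.1) | 0.5 | 0.000 | 0.709 | 0.579 |
| Weight (12, 0.1) | 0.8 | 0.000 | 0.971 | 0.912 |
| Weight (12, 1) | 0.5 | 0.014 | 0.694 | 0.537 |
| Weight (12, 1) | 0.8 | 0.055 | 0.977 | 0.900 |
| Energy intake (400, 1) | 0.5 | 0.000 | 0.707 | 0.592 |
| Energy intake (400, 1) | 0.8 | 0.000 | 0.971 | 0.902 |

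At d = 0 the ungrouped χ² rejected in 0% to 1.05% of trials, the t test in 4.3% to 5.55%, and the median-split χ² in 5.35% to 7.05%. The split figures are therefore slightly flattered.

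Coarser data help the ungrouped χ² a little. For HbA1c to one decimal with SD between 1.2 and 0.8, its power is about 1% to 4% at 0.5 SD and about 10% to 27% at 1 SD.

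**Step 4. The categorical half.** Pooled t test on 0/1 smoking data against χ², 10,000 simulations, 50 per group, assumed smoking proportions:

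| Proportions | χ² | t test |
|---|---|---|
| 30% v 30% | 0.0498 | 0.0498 |
| 30% v 15% | 0.441 | 0.437 |
| 40% v 20% | 0.600 | 0.600 |

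The two tests are practically interchangeable here.

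**The case against.** **It is probably a slip.** The sentence names two standard tests and two data types with one pair transposed, and an analyst may well do the right thing. This stands as a description of the likely cause. It does not remove the error: no other part of the document restores the pairing, and the list of descriptive summaries does not settle which test goes where.

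**The near-zero power depends on ungrouped values.** Anyone applying χ² to a continuous variable would usually group it first, and a median split keeps most of the power. This stands as a limit on the size of the harm. But the document states no grouping and no cut-points, and a median split still falls short of the t test.

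**An unseen analysis plan may cover it.** That would excuse missing detail. It does not excuse a sentence that names a test for each data type and names the wrong one.

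**Stronger readings that the document does not support.** A reader might infer that the trial cannot detect a glycaemic effect. That goes too far, since even the ungrouped χ² on HbA1c has some power at 1 SD and a grouped analysis has much more. A reader might take P = 0.45 as the expected result for HbA1c; it requires all 100 values to differ, which is implausible at one decimal. A reader might also count both halves of the swap as equally damaging; step 4 shows that they are not.

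**Conclusion.** Wrong as written. Section 2.7 pairs the tests with the wrong data types, and that pairing governs the P values of the four continuous rows of Table 1. Taken literally on ungrouped values, the loss is severe: at a 0.5 SD difference, about seven trials in ten would reach significance with the t test and at most about four in a hundred with χ². At 0.8 SD the comparison is 97% to 98% against 0% to 7.3%. These figures rest on assumed SDs, recording precision and normality, and on no prior grouping. The exact result in step 1 rests only on distinct values.

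The finding is that the stated method is incorrect and cannot be relied on. It is not a prediction that the trial will be analysed with near-zero power. The harm is confined to the continuous rows; the smoking row is essentially unaffected.

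**What to change.** Exchange the two test names in section 2.7, so that continuous variables are compared by independent t tests and categorical variables by χ² tests. If any continuous variable is meant to be analysed in categories, state the cut-points there. The cost is one corrected sentence, with no change to data collection or sample size.

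A baseline-adjusted model for the continuous outcomes and Fisher's exact test for sparse tables are optional additions. Neither follows from this error, and the correction should not wait for them.

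### Section 2.7 names only unadjusted two-sample tests and Table 1 gives no time point, so no use of baseline values is specified; with 50 per group this can cost precision, but it does not bias the comparison

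*Protocol article*

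**What the plan says.** Methods (section 2) fixes the design: "The patients will be randomly assigned into the study group and control group and each group includes 50 patients", and "The duration of follow up is 2 months".

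Statistical analysis (2.7) fixes the method, in a sentence that names χ² tests first and then "independent *t* tests, the analysis for continuous variables and categorical variables are implemented respectively". Read literally, this pairs χ² tests with continuous variables and t tests with categorical ones. The two are presumably transposed, and the rest of this point assumes so. No other test or model is named, and the significance threshold is .05 with sidedness unstated.

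The shell of Table 1 (Results) has a column headed "Study group (n = 50"), a matching control column and a P value. Its rows are body weight, current smokers, glycosylated hemoglobin, fasting blood-glucose and energy intake. It does not say whether cells hold values at 2 months, changes from baseline, or something else. Outcomes (2.6) does not help: it says only that the examinations are done in a timely way and names neither a baseline nor a final visit.

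**The concern.** Four of the five rows in Table 1 are continuous and can be measured both before the intervention and at 2 months. Where the two measurements are correlated, part of the spread at 2 months is predictable from the start. A t test on final values leaves that part in the error term, and it leaves any chance baseline difference between the groups in the estimate.

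The Discussion itself describes the sample as small and the follow-up as short. In such a trial it matters whether the analysis uses information that costs no extra patients. What is at stake is power and the width of the confidence interval. The validity of the test is not in question.

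**Working it through.** **Inputs from the protocol article.** 50 patients per group (section 2); threshold .05 (2.7); independent t test with no covariate (2.7).

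**Assumptions.** The article gives no effect size, SD, power or correlation, so there is no stated figure to reproduce. I assume a two-sided test, no dropout, a true difference d = 0.5 SD for illustration, equal variance at both times, and r from 0.2 to 0.8.

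**Step 1: t test on final values.** The standard error is SD × √(2/50) = 0.2 SD. The non-centrality is d × √(50/2) = 0.5 × 5 = 2.5. With 98 degrees of freedom, power is 69.7%. By the normal approximation, the difference detectable with 80% power is (1.960 + 0.842) × 0.2 = 0.56 SD.

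**Step 2: adjust for baseline.** The error variance is multiplied by 1−r², so d becomes d/√(1−r²). The equivalent unadjusted size is 50/(1−r²) per group.

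**Step 3: t test on change.** If Table 1 is meant to hold changes, the variance is 2(1−r) SD² and d becomes d/√(2(1−r)). The ratio of ANCOVA variance to change-score variance is (1−r²)/(2(1−r)) = (1+r)/2.

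| r (assumed) | 1−r² | Power, t test on final values | Power, t test on change | Power, ANCOVA | Equivalent unadjusted n per group | ANCOVA/change variance, (1+r)/2 |
|---|---|---|---|---|---|---|
| 0.2 | 0.96 | 70% | 50% | 71% | 52 | 0.60 |
| 0.3 | 0.91 | 70% | 55% | 74% | 55 | 0.65 |
| 0.5 | 0.75 | 70% | 70% | 82% | 67 | 0.75 |
| 0.6 | 0.64 | 70% | 79% | 87% | 78 | 0.80 |
| 0.7 | 0.51 | 70% | 89% | 93% | 98 | 0.85 |
| 0.8 | 0.36 | 70% | 97% | 98% | 139 | 0.90 |

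The degree of freedom that ANCOVA spends (97 rather than 98) does not alter these figures at the precision shown.

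**Step 4: a smaller effect.** With d = 0.4 SD, power is 51% for the t test on final values. With ANCOVA it is 63% at r = 0.5 and 79% at r = 0.7. The pattern does not depend on choosing 0.5 SD.

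**Reading.** Against final values, the gain is small when r is low and large when r is high. Against change scores it is the reverse. Across the assumed range ANCOVA is at least as powerful as either.

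**The case against.** **Baseline values are thrown away.** A reader might infer this, but the document does not say so. Neither 2.6 nor Table 1 names a time point, and an independent t test on change scores would fit 2.7 and would use the baseline. All that can be said is that no use of baseline is specified. The 70%-to-93% contrast at r = 0.7 holds only if final values are compared; on change scores it is 89% against 93%.

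**Baseline weight, glycosylated hemoglobin and glucose are available anyway.** The Diet section might be read this way, since it states "The patients risk profile is discussed and the individual goals for smoking cessation, exercise, and diet are set". But those goals concern smoking, exercise and diet. The risk profile is not defined, and the text does not show that these three measures are taken at baseline in both groups.

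**Much of the precision is lost.** This depends on r, which the document does not give. At r = 0.2 to 0.3 power moves only from 70% to between 71% and 74%.

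**Chance imbalance could match the treatment effect.** The document gives no effect or SD to support this. With a standard error of 0.2 SD, a baseline difference of 0.5 SD is 2.5 standard errors, about a 1.2% chance for any one variable. Smaller imbalances are common (above 0.2 SD in about 32% of trials), but randomisation already allows for them in the t test's error rate.

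**Covariates and table layout belong in an analysis plan.** Silence would be no finding. Here, however, the article states its tests and prints its table shell, so the choice can be assessed. That an unadjusted t test is legitimate stands in full, and it limits the point to efficiency.

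**Conclusion.** The point holds as a matter of efficiency. Section 2.7 fixes unadjusted two-sample tests, Table 1 leaves the time point open, and a better method is available at almost no cost.

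Against a t test on final values, adjustment removes 4% of the error variance at r = 0.2, 25% at r = 0.5 and 64% at r = 0.8. Against a t test on change it removes 25% at r = 0.5 and 10% at r = 0.8. These figures rest on assumed values of r, and the powers also on an assumed 0.5 SD difference. They apply to the four continuous rows and not to current smokers.

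A reader might go further and conclude that the planned comparison is biased or invalid. The document does not support that: patients are randomised, and the t test keeps its error rate. The change should be made, but the trial can be interpreted without it.

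**What to change.** In 2.7, analyse body weight, glycosylated hemoglobin, fasting blood-glucose and energy intake each by ANCOVA: the 2-month value on randomised group, with the baseline value of the same outcome as covariate. Keep a χ² test for current smokers. Correct the sentence that pairs tests with variable types while rewriting the section.

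Lay out Table 1 as baseline by group, 2 months by group, adjusted difference with 95% CI, and P value. This also settles what the cells contain.

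The cost is one degree of freedom per model, a few lines of text and a new table shell. SPSS, already named in 2.7, fits the model. The one possible addition in the clinic is that each outcome's baseline value must be recorded before the intervention in both groups, if this is not already planned. No extra patients are needed.
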